### Design

Individuals in the UIA follow-up cohort will be allocated to two groups, a modeling and a validation group, in a ratio of 2:1. Taking the annual rupture rate as 1% [2], the rate of loss would be less than 20%. The data will be analyzed statistically in the 5th years, the expectation being that at least 130 patients’ aneurysms will rupture in the first 4 years. The modeling group will be used to establish the risk of UIA rupture and compare relevant clinical information, radiological images, hemodynamic variables, genetic factors, HRMRI findings, and biomarkers [12, 13, 26–37] between the rupture and non-rupture groups to identify the risk factors for rupture. These will then be incorporated into a multi-dimensional model for predicting risk of UIA rupture. The validation group will then be used to validate that model (Fig. 2).

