This study will incorporate nested screening of 500 individuals from cohort 1 (CIAP-1). Recruitment for this study started in September 2016. The estimated primary completion date will be in December 2020. The project will produce preliminary results in the 5th year. After the end of the 5th year, we will have a longer follow-up visit to the patients who have been in the group.

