Risk factors for rupture, including hemodynamic variables, genes, and biomarkers will be calculated in a nested cohort study of the entire first cohort (CIAP-1: the first project of the China Intracranial Aneurysm Project and is managed by Tangdu Hospital, Fourth Military Medical University). A multi-dimensional model for predicting UIA rupture and bleeding that incorporates clinical, imaging, HRMRI data, and so on will be constructed by using a statistical model.Model validation: After establishment of the model, the second group of the follow-up cohort will be used for blind verification.Comparative analyses of histopathology of aneurysm walls: When participants undergo surgery for ruptured intracranial aneurysms, the sites of rupture will be identified intraoperatively and specimens of the aneurysm wall will be removed and preserved in formalin. The location of rupture, pathological damage, hemodynamic variables, HRMRI findings, and relevant biomarkers will be analyzed to identify differences between unruptured and unruptured aneurysms. Relationships between pathological damage, hemodynamic variables, and HRMRI features of the aneurysm wall will also be assessed.

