## Statistical methods

### Total sample size

CIAP-1: Calculation of the required sample size using an expected annual rupture rate of 1%, allowable error of d = 0.6%, and alpha = 0.05 on two-sided testing indicated that 1173 patients need to be enrolled per year, that is, 4692 over 4 years. An annual rupture rate of 1% [2] results in a loss rate of less than 20%. A reported hemodynamic index (complex flow patterns OR = 4.7) and HRMRI index (aneurysmal wall enhancement OR = 3.05 for ruptured versus unruptured aneurysm) also indicate that this sample size would be sufficient [12, 43]. Given that genetic factors have not yet been evaluated [35], our genetic testing will assess previously reported possible genetic indicators of prognosis; additionally, target genes and biomarkers will be selected according to the latest research progress in the future. In the 5th year of the study, we will analyze the data. As previously mentioned, at least 130 aneurysms are expected to rupture in the modeling group in the first 4 years. Allowing for a loss rate of 20%, the study will need to enroll 500 individuals.

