#### Evaluation of risk factors for aneurysms

Multiple regression analysis will be used to calculate OR values for high risk factors, including life habits and clinical and epidemiological data. Confidence intervals of 95% and cut-off values for sensitivity and specificity for predicting occurrence of an aneurysm rupture will be determined by receiver operating curves (ROCs). Next, the model will be used to assess risk of aneurysm rupture in the validation group and thus determine the model’s efficacy and accuracy. Finally, the model will be adjusted as indicated and established.

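### Any adjustment of the model after its test in the validation group would leave the final model without an independent test, and two sections disagree on whether validation comes before or after the model is established

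*Protocol article*

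**What the plan says.** The Design section creates two groups and no third: "Individuals in the UIA follow-up cohort will be allocated to two groups, a modeling and a validation group, in a ratio of 2:1". It gives the second group one task: "The validation group will then be used to validate that model".

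The model-building section (Model building, first set of UIA queues) repeats that role. Once the model has been established, "the second group of the follow-up cohort will be used for blind verification".

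The analysis section (Evaluation of risk factors for aneurysms) gives a different order. Regression and ROC cut-offs come first. Then: "Next, the model will be used to assess risk of aneurysm rupture in the validation group and thus determine the model’s efficacy and accuracy". The last step is: "Finally, the model will be adjusted as indicated and established".

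After that, the article mentions only further follow-up of the same people, under Data collection and management: "After the end of the 5th year, we will have a longer follow-up visit to the patients who have been in the group". It does not describe this as a re-validation.

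**The concern.** A held-out group gives an honest estimate of accuracy only for a model that was fixed before the group was opened. In the analysis section, accuracy is determined in the validation group and the model is finalised afterwards. The natural reading of the adjustment is that it responds to the validation result just obtained. Data that steer the model are development data. The model put forward for use would then differ from the model that was tested, and no untouched patients would remain to test it.

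The prediction model is the main product of CIAP-2. The abstract says it will give a preliminary basis for treating aneurysms at high risk of rupture. Readers need to know which version of the model the reported accuracy belongs to.

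**Working it through.** **Order of steps.** This part is textual and needs no arithmetic.

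| Section | Order stated |
|---|---|
| Design | build in modeling group, then validate in validation group |
| Model building | model established, then blind verification in the second group |
| Evaluation of risk factors | build, then measure accuracy in validation group, then adjust, then established |

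In Model building, establishment comes before validation. In Evaluation of risk factors, it comes after validation and after any adjustment. Both cannot hold. The article provides no third split, no external cohort and no resampling of an adjusted model. Under the analysis section's order, an adjusted model is therefore not tested again.

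**Size of the validation group.** No figure in the document depends on the order of steps. The counts below only show how much chance misfit an adjustment could respond to.

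Inputs from the document: 5000 patients in CIAP-1, 500 in the nested CIAP-2 sample, an annual rupture rate of 1%, 4 years, loss of up to 20%, and a 2:1 split. Assumption: every patient contributes 4 full years.

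The document's own event count comes first. Total sample size says "at least 130 aneurysms are expected to rupture in the modeling group in the first 4 years".

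- 5000 × 0.01 × 4 = 200 ruptures, and two thirds of these is 133. This matches the stated 130 only with no loss.
- With 20% loss, 200 × 0.8 = 160, and two thirds is 107.

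Validation third:

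- 5000 patients, no loss: 200 / 3 = 67 ruptures among 1667 patients, so 1600 without rupture.
- 5000 patients, 20% loss: 160 / 3 = 53 ruptures among 1333 patients, so 1280 without rupture.
- 500 patients, no loss: 500 × 0.01 × 4 = 20, and 20 / 3 = 7 ruptures among 167, so 160 without.
- 500 patients, 20% loss: 16 / 3 = 5 ruptures among 133, so 128 without.

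**Precision of the AUC.** Hanley-McNeil standard error, at an assumed AUC of A = 0.75:

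SE² = [A(1−A) + (n₁−1)(Q₁−A²) + (n₀−1)(Q₂−A²)] / (n₁n₀), where n₁ and n₀ are the numbers with and without rupture, Q₁ = A/(2−A) = 0.600 and Q₂ = 2A²/(1+A) = 0.643.

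Hence A(1−A) = 0.1875, Q₁−A² = 0.0375 and Q₂−A² = 0.0804.

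Worked for 53 v 1280: (0.1875 + 52 × 0.0375 + 1279 × 0.08036) / 67840 = 104.9 / 67840 = 0.00155. So SE = 0.0393, and 1.96 × SE = 0.077.

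| Ruptures v no rupture | 95% half-width |
|---|---|
| 67 v 1600 | 0.069 |
| 53 v 1280 | 0.077 |
| 7 v 160 | 0.21 |
| 5 v 128 | 0.25 |

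**The case against.** - **The adjustment is conditional.** It is to be made only as indicated. If none is made, the validated model and the final model are the same. This stands. A reader might infer that the final model will certainly never have been validated, but the text does not say that. It permits that outcome and sets no criterion for when an adjustment is called for.
- **One section already has the safe order.** Model building puts verification after establishment, which is close to a lock. This also stands. The document contradicts itself; it does not set out a settled plan to tune on the validation data.
- **Inflated accuracy is not planned.** A reader might infer that published performance will be too good. The text does not support that. Accuracy is determined before any adjustment, and that figure is an honest estimate for the model as built. Nothing says performance will be measured again in the same group, that the earlier figure will be attributed to the adjusted model, or whether the adjustment is a small recalibration or a full refit.
- **The harm may be modest in a large cohort.** An illustrative simulation assumed 10 predictors, 3 of them real with a log odds ratio of 0.4 per SD, about 4% events, and a full refit on the validation group as the worst case. With 1667 validation patients the AUC in new data was 0.67 after refitting and 0.68 without. The refitted model showed 0.71 when scored in the group it was fitted on. With 167 patients the refitted model showed 0.85 in that group and 0.58 in new data. The large gap needs the small-cohort reading, a full refit and re-scoring in the same patients.
- **Event counts.** A reader might infer far fewer validation ruptures, because enrolment is spread over 4 years. That needs a mean follow-up well below 4 years, which the document does not state.

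The objection that an article leaves such detail to a fuller plan does not succeed. The sequence is stated here, and it is stated in two incompatible ways.

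**Conclusion.** The point holds in conditional form. The analysis section allows the model to be changed after its accuracy has been measured in the only held-out group, and it conflicts with the model-building section on order. If an adjustment follows from the validation result, the final model has no independent test and the reported validation figures belong to the version before adjustment. Certain loss of validation, or certain over-statement of accuracy, goes beyond the text.

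The logical defect depends on no number. The calculated half-widths show that a disappointing validation result could be chance even on the favourable 5000-patient reading, and easily so if only the 500 nested patients are followed. They rest on the document's 1% rate and on the assumptions of 4 full years per patient and an AUC of 0.75.

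**What to change.** Reconcile Model building and Evaluation of risk factors with one statement. Predictors, coefficients and cut-off are locked before the validation group is opened, and the discrimination and calibration of that locked model are the reported validation result.

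If the model is updated afterwards, report the update separately and label it as not independently validated. Give it optimism-corrected performance from resampling that repeats the whole procedure, including the update. The bootstrap is one suitable choice.

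The cost is a sentence or two and a little more analysis work, with no new patients or data. The downside is that the performance figures may be less favourable. The change has to be made before the validation group is opened, because the group cannot be made untouched again.

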## Discussion

The study will comprise only Chinese individuals and incorporate Korja et al.’s recommendations for research on UIAs [44]. This study will be the first multicenter prospective registry study of a multidimensional model for predicting aneurysm rupture in China. In addition to the previous study of baseline data, this study will also explore hemodynamic factors, imaging factors, genomics, and biomarkers in more detail with the aim of making it more applicable to clinical situations. The assumption of rigid wall in the parent vessel and aneurysm may introduce bias in our simulation results. Image data and biochemical indicator of different centers will be standardized; however, data biases associated with different types of imaging machines and different detection methods are inevitable. Additionally, because this research includes only Chinese individuals, the results will be more applicable to Chinese people than to others; the applicability to other populations is unknown.

## Abbreviations

CIAP: China Intracranial Aneurysm Project
CFD: computational fluid dynamics
CRF: Case Report Form
CT: computed tomography
CTA: computed tomography angiography
DSA: digital subtraction angiography
EDC: Electronic Data Capture
HRMRI: high resolution magnetic resonance imaging
MRA: magnetic resonance angiography MRI: magnetic resonance imaging
SAH: subarachnoid hemorrhage
UIA: unruptured intracranial aneurysm
